### Outcome measures

The primary outcome measure of the DIABAR-trial is glycemic control, as measured by the difference in Hba1c 12 months after RYGB and OAGB. Glycemic control at 6 months, 2–5 and 10 years of follow-up, and the remission of T2DM at 1–5 and 10 years of follow-up are secondary outcome measures. For remission of diabetes, we will use the proposed definition according to ADA consensus report 2021 primarily (Hba1c < 6.5%), and in a secondary analysis, the more strict cut-off < 5.7% will be used [19]. Other secondary outcome measures are related to the interplay of obesity, NAFLD/NASH, and cardio-vascular performance. Table 1 shows the schedule of enrolment and study procedures (SPIRIT-format). All measurements will be performed by the researchers and physicians according to a standard operating procedure.

*Demographics* consist of age, sex, ethnic background, medical history, use of medication, history of weight-change, intoxications, educational level, employment status, and physical activity. Prior to surgery, patients will be asked about their expectations of metabolic surgery in terms of weight loss.

*Biometric data* consist of weight, height, waist to hip ratio, temperature, bioelectrical impedance (BIA), electrocardiogram (ECG), blood pressure, pulse, stroke volume, cardiac output, and systemic vascular resistance (Nexfin).

*Dutch versions of validated questionnaires* are used for evaluation of psychological measures. This includes quality of life, self-efficacy, hunger and craving, social support, depression, and body image, as previously described in the protocol of the BARIA-study [15]. Food intake is registered using food diaries. Gastro-intestinal complaints are assessed with the gastro-intestinal quality of life (GIQLI) questionnaire [20].

*Peripheral blood* will be drawn at various time points as part of the regular follow-up and includes hemoglobin, leukocytes, C-reactive protein, HbA1c, glucose, c-peptide (only baseline), electrolytes, kidney function, hepatic enzymes, lipid profile, iron, vitamins, and thyroid profile.

*Mixed meal test*, a 2-h oral mixed meal test (MMT), will be performed three times in the course of the study [21]. During the MMT, the patient will consume two 125 ml Nutridrink compact drinks (Nutricia®). At set time points during this test, blood will be obtained through an intravenous line and will be used to measure insulin sensitivity, plasma metabolites, and bile acids.

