### Statistical analysis

#### Power calculation and sample size

Sample size calculation was performed based on a retrospective analysis of patients after RYGB (*n* = 90) and OAGB (*n* = 37). Patients were matched in a 3:1 ratio on baseline age, BMI, and gender. The mean pre-operative Hba1c in the RYGB group was 7.5 ± 1.4% and 7.5 ± 1.5% in the OAGB group (*p* = 0.97). Null hypothesis is as follows: there is no difference in decrease of Hba1c at 12 months after RYGB or OAGB in patients with T2DM. Alternative hypothesis: the decrease in Hba1c after OAGB is higher than after RYGB in patients with T2DM at 12 months after surgery. For sample size calculation, the mean Hba1c of both groups was compared with a two-sided significance level of *P* < 0.05 and a power of 80%. Based on the retrospective results, 100 subjects per group will be required. Considering a 10% dropout rate, 220 patients are needed.

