#### Analysis of endpoints

The statistical analyses will be performed using SPSS statistical software (IBM corporation, New York, USA). Data will be expressed as mean, standard deviation, or median and range, as appropriate. Differences in categorical variables will be evaluated with the chi-square or the Fisher exact test, as appropriate; continuous data will be compared with the Student *t* test or Mann-Whitney *U*. Multivariate analysis and ANOVA for repeated measures will be used. *P*-values < 0.05 will be considered statistically significant. Clinical complications will be evaluated by an independent adjudication committee. An interim analysis will be performed at 60 patients per group. A modified intention to treat analysis will be performed (all randomized patients that initiate treatment in the arm they are allocated to, i.e., exempting those who do not undergo surgery at all) in which “last value carried forward” will be used for missing observations. A per-protocol analysis will be carried out as well to account for effects of revisional surgery (i.e., revision from OAGB to RYGB). For this analysis, only data of patients gathered before revisional surgery will be used.

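### Repeated-measures ANOVA needs a value at every visit, but the per-protocol analysis cuts the series short at revisional surgery; a mixed model would use the data the protocol keeps

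*Protocol article*

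**What the plan says.** All references are to the protocol article.

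- **Method for repeated data** (Analysis of endpoints): "Multivariate analysis and ANOVA for repeated measures will be used". The sentence does not name the outcome, the visits, the term tested or the handling of sphericity, and does not explain the multivariate analysis.
- **Other comparisons** (same section): "continuous data will be compared with the Student" t test or the Mann-Whitney U test. Significance is fixed as P-"values < 0.05 will be considered statistically significant". On software: "The statistical analyses will be performed using SPSS statistical software".
- **Missing data** (same section): the modified intention-to-treat analysis carries the last value forward.
- **Per-protocol analysis** (same section): it is meant to deal with revisional surgery, with conversion from OAGB to RYGB as the example, and it is restricted to measurements that precede the revision. No rule for missing values is attached to it.
- **Outcomes** (Outcome measures): the primary outcome is glycemic control "as measured by the difference in Hba1c 12 months after RYGB and OAGB". Secondary outcomes include "Glycemic control at 6 months, 2–5 and 10 years of follow-up".

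**The concern.** Repeated-measures ANOVA in its standard form works on complete rows: a patient without a value at one visit contributes nothing. The per-protocol rule produces incomplete rows by design, because a revised patient has values up to the revision and none after it. The named method and the data rule do not fit together.

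At stake is the long-term comparison of the two operations in the analysis meant to separate their effect from that of revision. If revised patients drop out of it, it becomes a comparison of never-revised patients. If revision is more frequent in one arm, that selection differs by arm. If their values are filled in instead, the analysis treats invented late values as measurements.

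A second, smaller worry is the sphericity assumption. Visits run from baseline through 6 months to 10 years, with gaps of six months to five years. If within-patient correlation decays with time, an uncorrected group-by-time F test rejects too often.

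**Working it through.** **1. Complete rows against truncated series.** Table 1 schedules regular laboratory work before surgery and at 6 months and 1, 2, 3, 4, 5 and 10 years, and Outcome measures lists HbA1c in that bloodwork. That gives 8 time points, 7 of them post-operative.

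Take a patient revised between the 2-year and 3-year visits (an illustration, not a figure from the protocol):

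- Values kept by the per-protocol rule: baseline, 6 months, 1 year, 2 years = 4 of 8.
- ANOVA on complete rows: uses 0 of these 4.
- ANOVA after carrying the last value forward: uses 8, of which 8 − 4 = 4 (3, 4, 5 and 10 years) are copies of the 2-year value.
- Mixed model on observed values: uses exactly the 4.

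If 5% or 10% of 100 patients in one arm were revised at that point (assumed rates), complete-row analysis would discard 5 × 4 = 20 or 10 × 4 = 40 HbA1c values that the protocol says to use.

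**2. Ordinary missed visits, where gaps are not filled.** If each post-operative visit is missed independently by 5% or 10% of patients (assumed), the share with all seven values is 0.95^7 = 0.70 or 0.90^7 = 0.48. This does not describe the modified intention-to-treat analysis, where carrying forward fills the gaps. It would apply to the per-protocol analysis if no filling is done there.

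**3. Type I error of the group-by-time test.** The only figure in the protocol is the nominal 5%. It gives no within-patient correlation and no follow-up SD, so all covariance structures below are assumptions. Setting: no true difference, 100 per arm (the evaluable number in the sample-size section), complete normal data, visits at 0, 0.5, 1, 2, 3, 4, 5 and 10 years, 8,000 runs each. The Monte Carlo standard error near 5% is √(0.05 × 0.95 / 8000) ≈ 0.24 percentage points.

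| Assumed correlation | Epsilon | Uncorrected F | Greenhouse-Geisser | Multivariate |
|---|---|---|---|---|
| Equal at all distances (compound symmetry) | 1.00 | 4.8% | 4.6% | 4.9% |
| Random slope | 0.79 | 6.4% | 4.9% | 5.2% |
| Random intercept + serial decay + visit noise, two settings | 0.84, 0.72 | 6.2%, 7.1% | 4.9%, 4.9% | 4.9%, 5.2% |
| Second of these settings, with larger baseline SD | 0.66 | 7.6% | 5.0% | 4.8% |
| First-order autoregressive by visit | 0.55 | 9.0% | 4.9% | 4.8% |
| Pure decay in time, 1-year correlation 0.5 to 0.9 | 0.69 to 0.42 | 7.6% to 9.9% | 4.9% to 5.3% | 4.6% to 5.7% |

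Shorter series inflate less, even uncorrected: 4.9% to 7.2% for baseline to 2 years and 5.0% to 6.1% for baseline to 12 months.

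**4. Primary outcome.** It is one comparison at one visit, so sphericity does not enter.

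**The case against.** The case against is strong on several points.

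- **A reader might infer that the long-term test will run at 7% to 10% instead of 5%.** The protocol does not support this. It nowhere says the F test will be uncorrected, and the same sentence names multivariate analysis. The choice of correction is a detail commonly left to the full protocol or analysis plan, which are not shown. Uneven spacing alone does not break sphericity either: equal correlation on the same visits gives about 5%.
- **A reader might infer that the main analysis loses 30% to 52% of patients.** It does not, because the modified intention-to-treat analysis carries values forward. Whether that imputation is sound is a separate question.
- **A reader might infer that no visit-specific comparison is planned.** The t test or Mann-Whitney U test in the same paragraph can supply one at each visit.
- **The sentence does not tie repeated-measures ANOVA to the per-protocol analysis or to the full HbA1c series.** That is true, so the point is conditional on its use there.

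The first three objections stand in full. The fourth limits the point without removing it: the article describes no other method for repeated data, and its per-protocol rule yields series that this method cannot take as they are. That conflict needs no assumption about correlation or about a correction.

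**Conclusion.** The point holds in a limited form. Repeated-measures ANOVA is poorly matched to the per-protocol rule. Revised patients would either be removed, with the pre-revision data the protocol keeps, or be completed with values never observed. Unequal loss by arm is possible, since the example of revision concerns OAGB, but no revision rates are given and the resulting bias cannot be quantified.

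The error-rate point is secondary. For an uncorrected group-by-time test over the 10-year series, type I error is about 5% to 10%. The upper part requires marked decay of correlation with time or a clearly larger baseline SD. With a Greenhouse-Geisser correction or a multivariate test it is nominal within simulation error.

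Only secondary longitudinal outcomes are concerned. This is a cheap improvement, not a fault in the trial's main result.

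**What to change.** For the secondary longitudinal outcomes, replace ANOVA for repeated measures with a linear mixed model:

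- visit as a category, treatment, treatment-by-visit and baseline-by-visit terms;
- unstructured covariance (7 post-operative visits give 7 × 8 / 2 = 28 parameters);
- all observed values, without carried-forward ones;
- the treatment difference with 95% CI at each visit named under Outcome measures;
- in the per-protocol analysis, pre-revision values only.

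The same model can serve weight and the questionnaire scores, over their own visits. It runs in the SPSS already named (MIXED procedure). If ANOVA is kept, state the sphericity correction or the multivariate test, and how truncated series enter.

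The cost is about one sentence in the analysis section, slightly more programming and no new data. The downside is reliance on a missing-at-random assumption: a revised patient's later course without revision must be predictable from the values already observed. Trial status expects recruitment to finish in 2024, so the 10-year data lie well ahead and the model can still be fixed before they are seen.

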### Ethics and permissions

The study will be conducted in accordance with the Declaration of Helsinki and “good clinical practice.” Ethical approval has initially been granted by the Institutional Review Board of Slotervaartziekenhuis en Reade, Amsterdam, the Netherlands. In 2019, the study was transferred to and approved by the Institutional Review board of Amsterdam UMC, location AMC, Amsterdam, the Netherlands (registered under NL61882.048.17). A data monitoring committee has not been installed. Auditing will be performed (at least) annually, independent from investigators and the sponsor.

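### The interim analysis at 60 per group has only a flat P < 0.05 rule and no stated purpose or boundary; if it can support an efficacy claim, the overall type I error is about 8%

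*Protocol article*

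**What the plan says.** Four statements in the protocol article bear on this.

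- **Analysis of endpoints, interim look.** "An interim analysis will be performed at 60 patients per group". No endpoint, purpose, stopping rule, boundary or division of alpha is given.
- **Analysis of endpoints, significance rule.** After listing the tests, the section says that P-values "< 0.05 will be considered statistically significant". No other level appears anywhere, and the interim is neither mentioned nor exempted.
- **Power calculation and sample size.** The group means of HbA1c are compared; the calculation "was compared with a two-sided significance level of" 0.05 with 80% power. The result is that "100 subjects per group will be required", raised to 220 in total for dropout. The interim plays no part in this calculation.
- **Ethics and permissions.** "A data monitoring committee has not been installed". The only independent committee named in the article adjudicates clinical complications. Independent auditing is planned, but it is not described as covering interim results.

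The primary outcome (Outcome measures) is the HbA1c difference at 12 months. The design is open, and the surgeon obtains consent, randomises and learns the allocation directly (Informed consent and randomization).

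**The concern.** A 5% test used at two looks, with success possible at either, has an error rate above 5%. The article puts an interim look in the section on endpoint tests and supplies one threshold. Someone who followed that section literally would test HbA1c at 0.05 with 60 per group and again at the end, and the two-sided 5% level behind the sample size would not hold.

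The primary claim is at stake. Under that use the false-positive rate is about 1.6 times the stated level (7.96 / 5 = 1.59). Estimates reported because an early look happened to be significant are also too large on average.

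A second issue is distinct from the first. In an open trial, knowledge of arm-level interim results can affect recruitment and follow-up, and the article names no independent body to receive them.

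**Working it through.** **Inputs**

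| Input | Value | Source |
|---|---|---|
| Threshold | 0.05, so \|Z\| > 1.96 | Analysis of endpoints |
| Sidedness, power | two-sided, 80% | Power calculation and sample size |
| Interim size | 60 per group | Analysis of endpoints |
| Final size | 100 evaluable, or 220/2 = 110 randomised, per group | Power calculation and sample size |
| Overall error rate after the interim | not stated | – |

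**Step 1. The plan's own sample size.** It cannot be derived forwards, because the article gives neither a target difference nor a 12-month SD. Solved backwards, the standardised difference is d = (1.960 + 0.842) × √(2/100) = 0.396. The pre-operative SDs are 1.4 and 1.5; assuming they also hold at 12 months, this is 0.55 to 0.59 HbA1c percentage points. For the total, 200 × 1.10 = 220 reproduces the stated figure. Nothing in this calculation allows for a second test.

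**Step 2. Overall error with two looks at 0.05.** Assume both looks test the primary endpoint, 60 per group have their 12-month value at the interim, and success can be claimed at either look. Under the null hypothesis the two Z statistics are bivariate normal with correlation √t, where t is the information fraction. The overall error is 1 − P(|Z1| < 1.96 and |Z2| < 1.96).

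- 60/100: t = 0.600, correlation 0.775, overall error 1 − 0.9204 = **0.0796**.
- 60/110: t = 0.545, correlation 0.739, overall error 1 − 0.9184 = **0.0816**.
- Other timings: 8.3% at t = 0.5 and 7.6% at t = 0.7.
- Check: 200,000 simulated trials with t tests at 60 and 100 per group gave 0.080 for either look and 0.050 for the final test alone.

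**Step 3. The other reading.** If the interim is for safety, description or futility only, just the final test can reject, and the error does not exceed 0.05.

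**Step 4. Boundaries that hold the level at t = 0.6**

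| Rule | Interim P | Final P | Overall |
|---|---|---|---|
| Haybittle-Peto | 0.001 | 0.05 | 0.0501 |
| O'Brien-Fleming spending (Lan-DeMets) | 0.0114 | 0.0457 | 0.0500 |

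The spending value at the interim is 2 × [1 − Φ(1.96/√0.6)] = 2 × [1 − Φ(2.530)] = 0.0114. Assuming a true effect of 0.40 SD, final-look power is 80.7% at 0.05 and 79.7% at 0.0457, a cost of about 1 point. With Haybittle-Peto the final-look power is unchanged.

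**Step 5. Exaggeration if an interim result is acted on.** This needs a true effect, which the article does not state. The value 0.40 SD is an assumption close to the back-solved 0.396. The interim mean of Z is d × √(60/2), and the mean estimate given |Z| > 1.96 follows from the truncated normal.

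| Assumed effect (SD) | Interim crosses 0.05 | Mean estimate when it does (SD) | Excess |
|---|---|---|---|
| 0.30 | 38% | 0.48 | 61% |
| 0.40 | 59% | 0.52 | 30% |
| 0.50 | 78% | 0.57 | 14% |

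**The case against.** The strongest reply is that 8% describes a trial the article never lays out. It requires that the interim tests 12-month HbA1c between arms, that it does so at 0.05, and that a stop or success claim may follow. The article states none of these. The 0.05 sentence is a general line closing a list of tests, and the sentence immediately before the interim one concerns adjudication of complications, so a safety look is an open reading. This is also a journal article: the full protocol, version 8.1, and any analysis plan are not shown and may contain a boundary.

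Much of this stands. A reader might infer that the trial's type I error simply is 8%; the article does not support that, because it gives the interim no efficacy role. A reader might also infer that the missing committee raises the error rate, or that the recruiting team will see the interim comparison. The first is wrong, since a committee does not enter the calculation. The second is unsupported, since no section says who performs or sees the analysis. The figures of 59% and 30% belong to an assumed effect.

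The reply does not remove the point. The article states a firm interim, a single level for significance and a sample size at that level. Applied together to HbA1c, these do not give 5%. If an unseen document has an efficacy boundary, it differs from the article's unqualified 0.05, and the article's wording still needs amending.

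**Conclusion.** The point holds conditionally. As written, the plan permits an interim efficacy test at an unadjusted 0.05 and does not exclude a claim or stop on it. On that use the overall two-sided type I error is 7.96% to 8.16%. The result assumes that 60 per group have 12-month data, that the final analysis has 100 to 110 per group, and that the test statistics are approximately normal. With no efficacy claim or stop at the interim, the stated 5% is kept.

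This is a needed clarification of a rule affecting the primary claim, not a demonstrated inflation. The absence of a monitoring committee in an open trial is a separate, unquantified concern about bias.

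**What to change.** Amend Analysis of endpoints to say one of the following:

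1. The look at 60 per group makes no between-arm efficacy test and allows no efficacy stop. The final test stays at 0.05, at no cost.
2. Efficacy is tested at P < 0.001 at the interim and P < 0.05 at the end: overall 5.01%, essentially no loss of power.
3. Efficacy is tested with O'Brien-Fleming spending, about 0.011 at the interim and 0.046 at the end for t = 0.6: overall 5.0%, about 1 percentage point of final-look power. The levels should be recalculated if the actual fraction differs; at 60/110 they are 0.0080 and 0.0469.

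Under any option, add that arm-level HbA1c results are withheld from the recruiting surgeons until the last 12-month visit, and say who receives the interim analysis.

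The change is one or two sentences. It is credible only if made before the interim comparison is seen. Trial status reports 86 + 14 = 100 patients enrolled at the two current centres, against 2 × 60 = 120 for the look, so timing matters.

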### Informed consent and randomization

Patients are first informed on the study during the preoperative screening program, which consists of consultations with a surgeon, an internist, a dietician, a psychologist, and meetings for patient education. If patients proceed towards surgery, they are screened for inclusion into the study. Patients are asked for written informed consent to participate in the study by the surgeon and also to store study materials in the DIABAR-biobank. After informed consent is obtained by the surgeon at the outpatient clinic, patients will be randomly assigned by the surgeon to undergo a RYGB or OAGB in a 1:1 ratio. Randomization will be performed with the use of electronic block-randomization with the program *Castor Electronic Data Capture* (Ciwit BV, the Netherlands). Block size varies between four and six; there is no stratification. Patients and surgeons are directly informed on the outcome of the randomization.

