## Discussion

The STAMPEDE-trial has shown that surgery is more effective than medical treatment in patients with obesity and T2DM [2]. Still, it has not been established which metabolic surgery is the most powerful in the treatment of T2DM. In the Netherlands, the RYGB is the most performed bariatric and metabolic procedure [23]. With a peri-operative mortality rate between 0.1 and 0.41%, a rate of serious adverse events within the first 30 days after surgery ranging from 1.38 to 8.3%, and sustainable weight loss at follow-up, the RYGB can be considered a safe treatment for severe obesity [24–30]. The remission of T2DM after RYGB is reported to be between 50 and 80% depending on length of follow-up [4, 5, 31–33]. Although the RYGB has good results, it is considered an advanced and complex laparoscopic procedure, with a learning curve between 50 and 100 cases [34]. The OAGB was introduced as a simplified version of the RYGB and from start the OAGB has reported promising results in terms of weight loss, post-operative morbidity and mortality [35–43]. In single-arms studies, the short-term remission of T2DM is reported to be between 84 and 92% [42, 43]. The DIABAR-trial will demonstrate which of these two procedures is the most beneficial in patients suffering from T2DM and severe obesity. This information will aid the patient and physician in selecting the most potent surgical treatment. By extension, it is important to weigh the metabolic advantages of these procedures against the concerns in the post-operative course. Besides the more obvious surgical complications, such as post-operative bleeding and anastomotic leakage, seen after both RYGB and OAGB, there are some procedure-specific concerns. Internal herniation (IH) is a potentially serious complication after RYGB as it harbors the risk of small bowel obstruction and subsequent small bowel ischemia; after OAGB, IH is seldomly seen [44–47]. The OAGB has been surrounded by controversy for its potential to cause biliary reflux and to induce subsequent metaplasia, dysplasia, and carcinoma of the gastric remnant and/or the esophagus [48, 49].

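### The modified intention-to-treat set is defined by two clauses that disagree about a randomised patient who receives the other operation at the index procedure

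*Protocol article*

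**What the plan says.** Under Analysis of endpoints, the article plans a modified intention-to-treat analysis and adds a per-protocol analysis, so the former is evidently the main one. Membership of the modified set is fixed in one parenthesis with two parts: "all randomized patients that initiate treatment in the arm they are allocated to, i.e., exempting those who do not undergo surgery at all". The first part admits "all randomized patients that initiate treatment in the arm they are allocated to". The second, introduced as a restatement of the first, describes the rule as "exempting those who do not undergo surgery at all".

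The per-protocol analysis in the same paragraph deals with later revisional surgery, with OAGB to RYGB as its example, and uses only data gathered before the revision. It does not mention a different operation at the index procedure.

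On timing and blinding, Informed consent and randomization says: "After informed consent is obtained by the surgeon at the outpatient clinic, patients will be randomly assigned by the surgeon". It then says: "Patients and surgeons are directly informed on the outcome of the randomization". Table 1 places allocation in the screening column, ahead of a separate visit within 42 days of surgery.

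**The concern.** The two parts are joined as if they named the same patients, and they do not. A patient allocated to OAGB who is given RYGB at the index operation has not started treatment in the allocated arm, yet has undergone surgery.

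If the first part governs, membership depends on which operation was done, after patient and surgeon already knew the allocation. That is a per-protocol-type set under an intention-to-treat label. If patients who switch differ in prognosis, and switching is more common in one arm, dropping them can bias the primary comparison.

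The rule is also better fixed before comparative data are seen. The trial is open and plans an interim analysis at 60 patients per group.

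**Working it through.** **1. The two parts compared, by type of randomised patient**

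| Randomised patient | First part | Second part |
|---|---|---|
| Receives the allocated bypass | in | in |
| Has no surgery | out | out |
| Receives the other bypass at the index operation | out | in |

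The conflict is confined to the third row.

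**2. Does anything else in the article settle the third row?** The per-protocol rule covers revision after the index operation only. Outcome measures says that patients undergo surgery according to randomization, which states an intention and not an analysis rule. The same section lists conversion as a surgical endpoint without saying whether that means the other bypass or open surgery. Nowhere does the article say that patients are analysed in the arm to which they were randomised.

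**3. The plan's own figures.** Power calculation and sample size gives 100 per group, two-sided 5%, 80% power, and 220 in total with 10% dropout (200 × 1.10 = 220). It states no effect size, so the 100 cannot be reproduced independently. Run backwards, the standardised difference that 100 per group can detect is

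√(2/100) × (1.960 + 0.842) = 0.396.

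The only SDs given are pre-operative, 1.4 and 1.5 HbA1c points. If they applied at 12 months, the detectable difference would be 0.396 × 1.4 = 0.555 to 0.396 × 1.5 = 0.594 points. At SD 1.45 it is 0.574.

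**4. Illustration of size. These inputs are assumptions, not taken from the article:** SD 1.45, 100 per arm, no true difference, crossover in the OAGB arm only at rate c, and crossovers whose HbA1c is g points worse than the rest of their arm.

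If the whole arm has mean 0, then (1 − c)m + c(m + g) = 0, so the patients who remain after exclusion have mean m = −c·g. The spurious arm difference is b = c × g, with standard error SE = 1.45 × √(1/100 + 1/(100(1 − c))). The two-sided type I error is 1 − Φ(1.96 − b/SE) + Φ(−1.96 − b/SE).

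Worked case, c = 0.05 and g = 1.0: b = 0.05; SE = 1.45 × √(0.01 + 1/95) = 0.208; b/SE = 0.241; type I error 0.0567.

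| Crossover c | g = 0.5: shift, type I | g = 1.0: shift, type I | g = 1.5: shift, type I |
|---|---|---|---|
| 2% | 0.010, 0.0503 | 0.020, 0.0511 | 0.030, 0.0524 |
| 5% | 0.025, 0.0517 | 0.050, 0.0567 | 0.075, 0.0651 |
| 10% | 0.050, 0.0565 | 0.100, 0.0762 | 0.150, 0.1098 |

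Against the detectable 0.574 points, the shifts run from 1.7% (0.010) to 26.1% (0.150). Keeping crossovers in the arm to which they were randomised leaves the type I error at 0.05.

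**5. What keeping them costs.** If crossovers have the RYGB result, the true effect is diluted to (1 − c) of itself, and power is Φ(2.802(1 − c) − 1.96):

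- c = 2%: Φ(0.786) = 78%
- c = 5%: Φ(0.702) = 76%
- c = 10%: Φ(0.561) = 71%

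**The case against.** The strongest reply is that the sentence has a natural benign reading. The second part says what the authors mean, and the only exclusion it names is patients without surgery. Together with the modified intention-to-treat label, this suggests patients who start surgery, analysed by allocated arm. Handling later revision in the per-protocol analysis fits that, since it implies that revised patients stay in the main set. This stands as the likelier intention. It does not remove the conflict, because the text does not say it and the first part says something else.

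The harm is also conditional. It needs both the literal reading of the first part and actual crossovers, and the article gives no crossover rate. That stands too. At 2% crossover the effect is negligible, and the 0.110 comes from the extreme corner of the table.

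Finally, the article condenses full protocol version 8.1, which is not shown and may handle crossovers. That would excuse silence, but here a rule is stated and its two halves disagree.

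A reader might infer more than the text supports:

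- That the trial has adopted a rule that drops crossovers and so breaks the randomised comparison. This follows only if the second part is ignored and crossovers occur.
- That the result would be an as-treated analysis. Neither part analyses patients by the operation received.
- That RYGB is the national standard to which patients would drift. The Discussion says only: "In the Netherlands, the RYGB is the most performed bariatric and metabolic procedure". It says nothing about switching.
- That patients know their arm for weeks before surgery. This is a plausible inference from Table 1, but no interval is stated.

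**Conclusion.** The inconsistency is real and is confined to patients who receive the other operation at the index procedure. It concerns a stated rule for the main analysis set, so it is not a detail left to another document. The literal first part would give a per-protocol-type set selected after an open allocation, while the second part would not.

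The size of any bias is unknown. Under the assumed inputs (crossover in one arm only, SD 1.45, crossovers 0.5 to 1.5 points worse), it is negligible at 2%, modest at 5% and potentially material at 10%. The documents do not show that any bias has arisen or will arise. They show that the rule allows two analysis sets and that one of them is open to bias.

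**What to change.** Remove starting treatment in the allocated arm as a condition for inclusion. State instead that all randomised patients in whom surgery is started are analysed in the arm to which they were randomised, whichever procedure was done or completed. Tying the set to surgery being started, and not to receipt of one of the two study operations, matters: the narrower wording would drop patients whose surgery was abandoned or changed to a third procedure, which again selects on the operation received.

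Report patients who never had surgery, and patients who received the other operation, by arm. Both halves of the present definition drop the former after an open allocation, so a sensitivity analysis of all randomised patients is a useful optional addition. It is not needed to resolve the inconsistency.

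The cost is one reworded sentence and two counts per arm. The statistical price is dilution of the effect and loss of power if crossovers are common, as shown in step 5 of the working.
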